# Beta‐blockers withdrawal in patients with heart failure with preserved ejection fraction and chronotropic incompetence: Effect on functional capacity rationale and study design of a prospective, randomized, controlled trial (The Preserve‐HR trial)

**DOI:** 10.1002/clc.23345

**Published:** 2020-02-19

**Keywords:** chronotropic incompetence, exercise capacity, heart failure with preserved ejection fraction, quality of life

## Abstract

**Background:**

The pathophysiology of heart failure with preserved ejection fraction (HFpEF) is complex and multifactorial. Chronotropic incompetence (ChI) has emerged as a crucial pathophysiological mechanism. Beta‐blockers, drugs with negative chronotropic effects, are commonly used in HFpEF, although current evidence does not support its routine use in these patients.

**Hypothesis:**

We postulate beta‐blockers may have deleterious effects in HFpEF and ChI. This work aims to evaluate the short‐term effect of beta‐blockers withdrawal on functional capacity assessed by the maximal oxygen uptake (peakVO2) in patients with HFpEF and ChI.

**Methods:**

This is a prospective, crossover, randomized (1:1) and multicenter study. After randomization, the clinical and cardiac rhythm will be continuously registered for 30 days. PeakVO2 is assessed by cardiopulmonary exercise testing (CPET) at 15 and 30 days in both groups. Secondary endpoints include quality of life, cognitive, and safety assessment. Patients with stable HFpEF, functional class New York Heart Association (NYHA) II‐III, chronic treatment with beta‐blockers, and ChI will be enrolled. A sample size estimation [alfa: 0.05, power: 90%, a 20% loss rate, and delta change of mean peakVO2: +1.2 mL/kg/min (SD ± 2.0)] of 52 patients is necessary to test our hypothesis.

**Results:**

Patients started enrolling in October 2018. As January 14th, 2020, 28 patients have been enrolled. It is projected to enroll the last patient at the end of July 2020.

**Conclusions:**

Optimizing therapy that improves functional capacity remains an unmeet priority in HFpEF. Deprescribing beta‐blockers in patients with HFpEF and ChI seems a plausible intervention to improve functional capacity. This trial is an attempt towards precision medicine in this complex syndrome.

**Trial registration:**

http://clinicaltrials.gov: NCT03871803.

AbbreviationsChIchronotropic incompetenceCPETcardiopulmonary exercise testingHFheart failureHFpEFheart failure with preserved ejection fractionHFrEFheart failure with reduced ejection fractionNYHANew York Heart AssociationPeakVO2peak exercise oxygen uptakeQoLquality of life

## INTRODUCTION

1

Heart failure (HF) with preserved ejection fraction (HFpEF) is a heterogeneous syndrome that is the predominant form of HF in western countries.^1^, ^2^, ^3^, ^4^ Chronotropic incompetence (ChI), defined as the inability to increase heart rate during exercise adequately, is commonly present (ranging from 20 to 75%) in HFpEF patients.^5^, ^6^, ^7^, ^8^, ^9^, ^10^, ^11^ Furthermore, ChI has been proposed as a pathophysiologic mechanism associated with poorer outcomes and decreased functional capacity in a subgroup of patients with HFpEF.^8^, ^12^, ^13^

Data from current registries show a high proportion (ranging from 50% to 80%) of beta‐blockers prescription in HFpEF patients regardless of the heart rhythm.^3^, ^14^ Nevertheless, there is no well‐established evidence endorsing the effect of beta‐blockers. For instance, recent studies suggested that patients with an ejection fraction of 50% or greater did not see any benefits from receiving beta‐blockers.^15^, ^16^, ^17^ Even more, the evidence is missing stratifying patients with HFpEF across ChI status.

When ChI is present, beta‐blockers may have negative effects on functional capacity and other surrogates of the disease severity by exacerbating the ChI. Thus, we hypothesize that deprescribing beta‐blockers in this particular scenario will translate into an improvement in short‐term maximal functional capacity. The purpose of this randomized controlled study is to evaluate the short‐term effects of beta‐blockers withdrawal on the functional capacity, cognitive function, and quality of life (QoL) in patients with HFpEF and documented ChI.

The primary endpoint of the study is absolute and relative changes in peak oxygen uptake (peakVO2) at 15‐day after the intervention. The secondary endpoints are: (a) 15‐day absolute changes in cognitive function assessed by the Mini‐Mental State Examination (MMSE) and Montreal Cognitive Assessment (MoCa); (b) 15‐day absolute changes in echocardiogram parameters (E/E' ratio and left atrial volume index); (c) 15 days absolute changes in QoL assessed by Minnesota Living With Heart Failure Questionnaire (MLHF); and (d) 15 days absolute and relative changes in prognostic biomarkers (N‐terminal pro‐B‐type natriuretic peptide ‐NT‐proBNP‐ and serum carbohydrate antigen 125‐CA125‐).

Safety endpoints include the composite event of the total number of episodes of acute HF hospitalizations, total episodes of worsening HF not requiring hospitalization or mortality at 6 months.

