### Study design

2.1

This study is designed as a multicenter, prospective, controlled, randomized, two‐arms, cross‐over, efficacy trial. The population includes patients with the diagnosis of stable HFpEF according to criteria of the European Society of Cardiology^18^ and New York Heart Association functional (NYHA) class II‐III/IV. A computer‐generated randomization sequence previously designed will be used to allocate participants (in a 1:1 ratio) to receive: (a) withdrawal of beta‐blocker followed by beta‐blocker reintroduction in two periods of 15 days; or (b) continuation of beta‐blocker followed by beta‐blocker withdrawal in two periods of 15 days. A summary of the study design is described in Figure 1. The study will be conducted in two centers in Spain. Discounting the time due to staggered entry, the total duration of a patient's follow‐up will be 6 months. All patients will provide signed informed consent before randomization. The research ethics committee approves the protocol of our center following the principles of the Declaration of Helsinki and national regulations.

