#### Treatment intervention and visits

2.3.2

Following screening (visit 0) and randomization (visit 1) visits, the procedures across treatment arms are:

*‐A‐arm*: Patients allocated to this arm are instructed to reduce by half the dose of beta‐blocker (Figure 1). The patients will be advised for potential adverse effects and instructed to contact with outpatient's clinics of HF if any adverse effect occurs. Patients will be checked in 3 days (visit 2) by a cardiologist. If clinically stable, the patients are instructed to withdraw the beta‐blocker and repeat all the procedures of the study at 15 days (visit 3). After visit 3, the patients initiate the previous half dose of beta‐blockers. Patients are visited at 18 days (visit 4). If clinically stable, the patient will increase to the previous dose of the beta‐blocker and repeat all the examination tests at 30 days (visit 5).

*‐B‐arm*: Patients allocated to this arm will continue with the same treatment and revisited 3 days after (visit 2) (Figure 1). All of the study procedures repeated at 15 days (visit 3), and, after them, the patients are instructed to reduce by the half dose of beta‐blocker. Likewise, the patients are advised for potential adverse effects and instructed to contact outpatient HF‐clinics of HF if any adverse effect occurs. Patients are revisited in 3 days (at 18 days, visit 4), and if clinically stable, the patient withdraws the beta‐blocker and repeats all the examination tests at 30 days (visit 5).

At visit 5, the responsible cardiologist will assess all the examination test and individually decide the convenience of beta‐blockers reintroduction or withdrawal in both arms. A cardiologist of the HF‐unit will clinically evaluate all patients at 60‐day after randomization (visit 6). Additional visits will be permitted according to the patient's clinical status and will be registered.

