### Statistical plan

2.6

Continuous variables will be presented as mean ± SD or median (interquartile range—IQR) as appropriately; categorical variables as percentages. All statistical comparisons will be made under the intention‐to‐treat principle. A repeated‐measures analysis of variance (ANOVA) will be used for the comparisons of continuous outcomes among the two‐intervention groups. The interaction group*time‐points will be tested to unveil any effect of time (15 and 30 days) on the magnitude of the intervention. Only in the event of imbalance in baseline characteristics, repeated‐measures analysis of covariance (ANCOVA) will be used. A two‐sided *P*‐value of <0.05 will be considered to be statistically significant for all analyses. All analyses will be performed with Stata 14.1.

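### The safety composite runs to 6 months, but the randomised arms differ only in the order of two 15-day periods, so comparing arms at that horizon cannot isolate the effect of withdrawal

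*Protocol article*

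**What the plan says.** All sources are in the Protocol article.

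- **Endpoint (Introduction).** The safety composite is the number of acute HF hospitalizations, "total episodes of worsening HF not requiring hospitalization or mortality at 6 months". Study design gives the same horizon: "the total duration of a patient's follow‐up will be 6 months".
- **Randomised contrast (Study design).** One arm has "withdrawal of beta‐blocker followed by beta‐blocker reintroduction in two periods of 15 days"; the other has "continuation of beta‐blocker followed by beta‐blocker withdrawal in two periods of 15 days".
- **Dose steps (Treatment intervention and visits).** Withdrawal goes through a half-dose step that lasts until a check 3 days later, in arm A from day 0 and in arm B from day 15. Reintroduction in arm A also has a half-dose step, from day 15 to day 18.
- **After day 30 (same section).** At visit 5 the responsible cardiologist reviews all the tests and will "individually decide the convenience of beta‐blockers reintroduction or withdrawal in both arms".
- **Comparison rule (Statistical plan).** "All statistical comparisons will be made under the intention‐to‐treat principle". The one named method, repeated-measures ANOVA, is for continuous outcomes. No method is named for the safety composite.

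**The concern.** A safety endpoint can inform on an intervention only over a span in which randomisation makes the arms differ in exposure to it. Here that span is days 0-15 and, reversed, days 15-30. By day 30 both arms have been through withdrawal. For the remaining five months exposure depends on a clinical decision made with the test results in hand.

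The article presents withdrawal as a possible treatment option for these patients, and decompensation and death are its declared safety outcomes. If the 6-month composite is compared by assigned arm, similar counts are the likely result even if withdrawal causes harm, and they could be taken as reassurance. If the counts differ, the difference may come from choices made after day 30, and its direction may mislead.

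**Working it through.** The article gives no event rate, power or sample size for the safety composite, so there is no figure of its own to reproduce. The check is of exposure.

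**1. Planned exposure to day 30**, from Treatment intervention and visits, assuming every patient is stable at each 3-day check:

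| Arm | Days 0-3 | Days 3-15 | Days 15-18 | Days 18-30 | Off | Half dose | Full dose |
|---|---|---|---|---|---|---|---|
| A | half | off | half | full | 12 | 3 + 3 = 6 | 12 |
| B | full | full | half | off | 12 | 3 | 3 + 12 = 15 |

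Difference in fully-off days, A minus B: 12 − 12 = 0.

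**2. Share of follow-up on non-randomised treatment.** With 6 months as 180 days, (180 − 30)/180 = 83%. With 182.5 days, as used below, 152.5/182.5 = 84%.

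**3. Expected event ratio A/B to 6 months.** Let r be the event rate off drug relative to on drug, and count a half-dose day as half the effect, (1 + r)/2 (assumption). Let p be the share of time off drug after day 30. In on-drug day equivalents:

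- Arm A: 12 + 6(1 + r)/2 + 12r + 152.5[1 + p_A(r − 1)]
- Arm B: 15 + 3(1 + r)/2 + 12r + 152.5[1 + p_B(r − 1)]

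For r = 2 the first 30 days give 12 + 9 + 24 = 45 in arm A and 15 + 4.5 + 24 = 43.5 in arm B.

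| Off drug after day 30, A v B (assumed) | Arm A | Arm B | A/B |
|---|---|---|---|
| 50% v 50% | 45 + 228.75 = 273.75 | 43.5 + 228.75 = 272.25 | 1.01 |
| 40% v 60% | 45 + 213.5 = 258.5 | 43.5 + 244 = 287.5 | 0.90 |
| 25% v 75% | 45 + 190.625 = 235.625 | 43.5 + 266.875 = 310.375 | 0.76 |
| 0% v 100% | 45 + 152.5 = 197.5 | 43.5 + 305 = 348.5 | 0.57 |

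With equal shares (50% v 50%), A/B stays between 0.995 and 1.008 for r from 0.5 to 3. Without the half-dose steps it is exactly 1.

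In the last three rows a doubling of risk off drug appears as fewer events in arm A, the arm labelled as withdrawal, because arm B is the one off drug at day 30.

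**4. Power of a 6-month comparison**, with 26 per arm, an assumed 0.2 to 0.8 events per patient per 6 months on drug, r = 2, and a normal approximation to the log ratio of two Poisson counts: 5% at 50% v 50%, 8-19% at 25% v 75%, and 19-58% at 0% v 100%. The first figure is just the type I error rate.

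**5. Days 0-15 alone, r = 2.** Arm A: 3 × 1.5 + 12 × 2 = 28.5; arm B: 15; ratio 28.5/15 = 1.9. The signal is nearly intact and in the expected direction. Events are few: at 0.2 per 6 months, 26 × 0.2 × 28.5/182.5 = 0.8 in A and 26 × 0.2 × 15/182.5 = 0.4 in B; at 0.8 per 6 months, 3.2 and 1.7. That is about 1 to 5 events in all.

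**The case against.** **The article does not state a between-arm test of the composite.** This is correct. The Introduction says what is counted, and the named method is for continuous outcomes. Tabulation of safety events is often left to an analysis plan, which is not shown, so its absence here is no fault. What stands is narrower: the horizon, the crossover, the free choice at day 30 and the intention-to-treat rule for all comparisons are stated, and together they point to a contrast of sequences.

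**A reader might infer that a 6-month arm comparison carries no information.** The documents do not support that. It would need treatment after day 30 to be independent of arm, which is nowhere stated, and the arms reach visit 5 in opposite states. Some signal may leak in, as the working shows. It would come from individual decisions, not from randomisation.

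**A reader might infer identical exposure of 15 days off and 15 days on.** That is nominal. Fully-off time is equal at 12 days, but half-dose and full-dose days are not.

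**A reader might infer that events after the day-60 visit go uncollected.** The article states 6 months of follow-up and allows further registered visits, and the flow chart is not available here, so this cannot be concluded.

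**Counting events to 6 months is legitimate monitoring** in patients who are all planned to undergo withdrawal. This is accepted. The objection is to an inference between arms, not to the collection.

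**Attribution by period has its own weakness.** No washout is described, so a decompensation started by withdrawal in arm A may appear after day 15 and be counted against beta-blocker. The fix has to allow for this.

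**Conclusion.** The point holds as a limit on what the 6-month composite can show. Compared by randomised arm, it contrasts two orders of the same treatments, followed by about 150 of 180 days (83%) on individually chosen treatment. The expected A/B ratio is about 1.00 for any true effect of withdrawal if treatment after day 30 does not depend on arm. If it does depend on arm, the contrast is non-randomised and may run opposite to the arm labels. A null result cannot support the safety of withdrawal.

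The exposure count rests on the planned schedule being followed. The ratios and power figures also rest on assumed values for r, the half-dose effect, the event rate and the shares off drug after day 30. The reading that arms would be compared rests on the general intention-to-treat sentence. The primary peakVO2 endpoint is not affected. The change should be made before the safety data are analysed.

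**What to change.** Reword the safety endpoint and its analysis as follows:

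1. **Randomised comparison:** events with onset in days 0-15, between arms as allocated.
2. **Supportive tabulation:** events in days 0-30 by treatment period (withdrawal or beta-blocker), shown separately by arm, with a note that arm A events after day 15 may be carry-over from withdrawal.
3. **Days 30-180:** events described by treatment actually taken after visit 5, labelled non-randomised, with no test between arms. The report should say that the choice was made after the test results were seen.
4. **Interpretation:** state in advance that similar 6-month totals by arm are not evidence that withdrawal is safe.

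The cost is wording and a re-tabulation by event date and treatment dates; no new visits or procedures are needed. The downside is sparse data: with few events in 15 to 30 days, the safety statement becomes essentially descriptive, with wide intervals.

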## METHODS

2

### Study design

2.1

This study is designed as a multicenter, prospective, controlled, randomized, two‐arms, cross‐over, efficacy trial. The population includes patients with the diagnosis of stable HFpEF according to criteria of the European Society of Cardiology^18^ and New York Heart Association functional (NYHA) class II‐III/IV. A computer‐generated randomization sequence previously designed will be used to allocate participants (in a 1:1 ratio) to receive: (a) withdrawal of beta‐blocker followed by beta‐blocker reintroduction in two periods of 15 days; or (b) continuation of beta‐blocker followed by beta‐blocker withdrawal in two periods of 15 days. A summary of the study design is described in Figure 1. The study will be conducted in two centers in Spain. Discounting the time due to staggered entry, the total duration of a patient's follow‐up will be 6 months. All patients will provide signed informed consent before randomization. The research ethics committee approves the protocol of our center following the principles of the Declaration of Helsinki and national regulations.

**Figure 1 clc23345-fig-0001:**
[figure not shown]
Flow chart for patient inclusion and follow up. BB, beta‐blockers

### Study population sampling

2.2

Candidate patients will be selected from the outpatient HF‐clinics of the Hospital Clínico Universitario of Valencia‐Spain and Hospital Clínico Universitario de Santiago‐Spain. Treatment will be following current guidelines^18^ and HF educational programs of each institution. Briefly, HFpEF is defined as the presence of: (a) symptoms and signs of HF with normal (≥50%) left ventricular ejection fraction (LVEF); (b) elevation of natriuretic peptides; and (c) increase in LV wall thickness and/or increased left atrial (LA) size as a sign of increased filling pressures. Inclusion and exclusion criteria are summarized in Table 1. Inclusion criteria require the presence of ChI after performing the cardiopulmonary exercise testing (CPET). The chronotropic index is equal to (heart rate at peak exercise−resting heart rate)/([220 – age] − resting heart rate).^19^ ChI is defined as a chronotropic index <0.62.

**Table 1 clc23345-tbl-0001:** Inclusion and exclusion criteria

Inclusion criteria	Exclusion criteria
Stable symptomatic heart failure (NYHA functional class ≥II) during the last month.	Inability to perform a valid baseline exercise test
Diagnosis criteria of HFpEF according to ESC guidelines: (a) symptoms and signs of HF (b) left ventricular ejection fraction >50% by Simpson method (c) NT‐proBNP >125 pg/mL in the last month (d) at least one additional criterion: 1. relevant structural heart disease (LVH and/or LAE); and/or 2. diastolic dysfunction	Significant primary pulmonary disease; including pulmonary arterial hypertension, chronic thromboembolic pulmonary disease or chronic obstructive pulmonary disease
	Patient with prior history of left ventricular ejection fraction <50%
	History of an acute coronary syndrome in the previous 12 months
Adults >18 years old	Effort angina or signs of ischemia during CPET
Previous admission for acute heart failure	Significant primary moderate to severe valvular disease
Previous treatment with beta‐blockers during the last 3‐month	Any other comorbidity with a life expectancy lower than 1 year
	Chronic treatment with digitalis or calcium channel blockers
Chronotropic incompetence assessed by CPET, defined as: [(HRmax − HRrest)]/[(220 − age) − (HRrest)] < 0.62	HR at rest >75 bpm
	Uncontrolled blood pressure, defined as systolic blood pressure > 140 mmHg and/or diastolic blood pressure > 90 mmHg.

Abbreviations: CPET, cardiopulmonary exercise testing; ESC, European Society of Cardiology; HF, heart failure; HFpEF, heart failure with preserved ejection fraction; HRmax, heart rate at maximum effort; HRrest, heart rate at rest; LAE, left atrial enlargement; LVH, left ventricular hypertrophy; NT‐proBNP, N‐terminal prohormone of brain natriuretic peptide; NYHA, New York Heart Association.

### Intervention

2.3

#### Eligibility assessment and screening visit

2.3.1

After reviewing the inclusion/exclusion criteria and signing the informed consent form, a comprehensive medical history, physical examination, anthropometry, and examination tests will be performed by two blinded cardiologists to patients' allocation groups. The examination tests will include an electrocardiogram (ECG), two‐dimensional transthoracic echocardiography, CPET, cognitive assessment by MMSE and MoCa, QoL assessment by MLHF, continuous ECG recording during the first 30‐day and blood samples for a panel of baseline biomarkers.

Finally, if the patients fulfill all the inclusion criteria (including ChI assessed by CPET) and any exclusion criteria (including a valid CPET without signs of ischemia), are randomized in a 1:1 ratio to one of the following interventions: (a) A‐arm: beta‐blockers withdrawal; or (b) B‐arm: beta‐blockers continuation.

#### Treatment intervention and visits

2.3.2

Following screening (visit 0) and randomization (visit 1) visits, the procedures across treatment arms are:

*‐A‐arm*: Patients allocated to this arm are instructed to reduce by half the dose of beta‐blocker (Figure 1). The patients will be advised for potential adverse effects and instructed to contact with outpatient's clinics of HF if any adverse effect occurs. Patients will be checked in 3 days (visit 2) by a cardiologist. If clinically stable, the patients are instructed to withdraw the beta‐blocker and repeat all the procedures of the study at 15 days (visit 3). After visit 3, the patients initiate the previous half dose of beta‐blockers. Patients are visited at 18 days (visit 4). If clinically stable, the patient will increase to the previous dose of the beta‐blocker and repeat all the examination tests at 30 days (visit 5).

*‐B‐arm*: Patients allocated to this arm will continue with the same treatment and revisited 3 days after (visit 2) (Figure 1). All of the study procedures repeated at 15 days (visit 3), and, after them, the patients are instructed to reduce by the half dose of beta‐blocker. Likewise, the patients are advised for potential adverse effects and instructed to contact outpatient HF‐clinics of HF if any adverse effect occurs. Patients are revisited in 3 days (at 18 days, visit 4), and if clinically stable, the patient withdraws the beta‐blocker and repeats all the examination tests at 30 days (visit 5).

At visit 5, the responsible cardiologist will assess all the examination test and individually decide the convenience of beta‐blockers reintroduction or withdrawal in both arms. A cardiologist of the HF‐unit will clinically evaluate all patients at 60‐day after randomization (visit 6). Additional visits will be permitted according to the patient's clinical status and will be registered.

